**FIGURE 1 F1:**
[figure not shown]
The flowchart of the trial.

This is a multicenter, double-blinded, randomized controlled trial (RCT) of two parallel groups. A total of 240 cases will be recruited by recruitment advertisements and introductions from clinicians at outpatient or inpatient departments. Patients who meet the inclusion criteria will be informed of the possibility of participating in this study at the outpatient clinic or at admission. A face-to-face interview will be arranged to inform the patients about the purpose, interventions, examinations and follow-up procedures of this study. After informed consent acquisition, patients will be randomized to the SJZD group or placebo group at a ratio of 1:1. An intervention phase with a 12-month treatment with SJZD granules or placebo will be implemented for recruited patients. Endoscopy will be conducted at the end of the intervention phase and 1 year later. The duration of follow-up is 24 months with 5 visits, and the schedule details are listed in Table 2.

**TABLE 2 T2:** Schedule of trial.

	Period					
Study phase	Enrollment	Visit 1	Visit 2	Visit 3	Visit 4	Visit 5
		3 months of interventions	6 months of interventions	9 months of interventions	12 months of interventions	The second year after intervention
Informed consent form	**√**					
Demographic information	**√**					
Inclusion and exclusion criteria	**√**					
General information	**√**					
Vital signs	**√**	**√**	**√**	**√**	**√**	**√**
Spleen deficiency rating scale	**√**	√	√	√	√	√
Endoscopy	**√**				√	√
Histological tests*	**√**				√	√
Routine blood tests	**√**	√	√	√	√	
Routine urine test	**√**	√	√	√	√	
Routine stool test	**√**	√	√	√	√	
Liver function	**√**	√	√	√	√	
Renal function	**√**	√	√	√	√	
Electrocardiograph	**√**	√	√	√	√	
Serum and stool samples collections	**√**				√	√
Adenomatous tissue collections*	**√**				√	√
Adverse events		√	√	√	√	√
Release drugs/placebo	**√**	√	√	√		
Retrieve empty packages			√	√	√	
Drug combination	**√**	√	√	√	√	√

Notes: Patients who are detected to find recurrence of colorectal adenoma and meet the criteria of resection are undergone endoscopy. Adenomatous tissue will be collected according to the relevant regulations and histology will be confirmed by pathological experts.

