### Outcomes

The primary outcome is the recurrence rate of CRA between the SJZD group and the placebo group at the first year after CRA removal. The number, size and location of adenomas will be recorded. Pathological type will also be recorded if recurrent adenomas meet the criteria for resection. Secondary outcomes include the following: 1) the recurrence rate of CRA at the second year post-polypectomy; 2) the pathological type of adenoma detected at either of the two endoscopies; and 3) the changes in spleen deficiency PRO scores after intervention.

Safety outcomes will comprise physical examinations, vital signs and laboratory examinations at every visit and AEs during the intervention phase. Laboratory indices will include routine blood tests, routine urine tests, routine stool tests, liver function tests, renal function tests and electrocardiograms. In the event of AEs, the onset time, symptoms and signs, duration of event and abnormal laboratory indicators or imaging results will be recorded. The definition and grade assessment of AEs are in accordance with the National Cancer Institute Common Terminology Criteria for Adverse Events (Version 5.0) (SERVICES USDOHAH, 2017).

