### Data collection and registration

Data will be recorded in CRF and then entered and stored in REDcap (http://longhua.site/redcap3), a web-based electronic database. All clinical investigators will be trained on how to communicate with patients and how to collect and input information into the electronic database. A total of five visits will be conducted in this trial. Investigators will obtain the informed consent of participants, and then assess the general and demographic information, collect their biomedical and adenomatous information at baseline. They will provide participants with 3 months of drugs/placebo from enrollment to the third visit. For visit 2∼visit 4, patients will be asked to return the empty packages to confirm drug compliance. Telephone calls will be arranged every month to contact patients about their feelings, AEs and adherence to the study. Adenomatous tissue will be collected endoscopically and stored according to the regulations and requirements of the pathological department at visit 4 and visit 5. Original data and collected samples will be preserved at least 5 years after closure of the trial. An independent data monitoring committee (DMC) will be established and will include clinical epidemiologists, data monitors, and statisticians who are not involved in the trial and are independent from sponsors. No competing interest will exist. They will review the documents, check CRFs and relevant data every 6 months to monitor the safety of the study, ensure the authenticity of the profiles and protect confidentiality of participants information. DMC will give suggestions on the study design revision or trial termination.

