### Statistical analysis

SAS statistical software will be used to analyze the data. The efficacy and safety of this study will be analyzed by the principle of intention-to-treat (ITT). The missing data will be filled by the method of the last observation carried forward. The measurement data will be expressed as the mean ± standard deviation or median (quartile interval) determined by whether the data are normally distributed and the variance is uniform. χ^2^ tests will be used to compare the primary and secondary endpoints between the SJZD group and the placebo group. The paired *t*-test and independent sample *t*-test will be used for intragroup comparison and intergroup comparison, respectively. Logistic regression analysis will be used for the factors affecting the recurrence rate. Interim analysis will be arranged when 50% of the sample is collected. Sub-group analyses will be determined based on characteristics of participants such as gender, body mass index or previous history of gastrointestinal diseases. *p* < 0.05 is considered statistically significant.

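### The second-year recurrence rate has no counting rule, and carrying the Visit 4 status forward into a missing Visit 5 gives a wrong rate under either reading

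*Protocol article*

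**What the plan says.** The Outcomes section sets the primary outcome as "the recurrence rate of CRA between the SJZD group and the placebo group at the first year after CRA removal" and the first secondary outcome as "the recurrence rate of CRA at the second year post-polypectomy". Study design and setting fixes the two examinations: "Endoscopy will be conducted at the end of the intervention phase and 1 year later". These are Visit 4 (month 12) and Visit 5 (about month 24).

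Removal of recurrent lesions is conditional. Outcomes says "Pathological type will also be recorded if recurrent adenomas meet the criteria for resection". The notes to Table 2 say "Patients who are detected to find recurrence of colorectal adenoma and meet the criteria of resection are undergone endoscopy", which is garbled but points the same way. Data collection and registration adds "Adenomatous tissue will be collected endoscopically and stored according to the regulations and requirements of the pathological department at visit 4 and visit 5".

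Statistical analysis states that chi-square "tests will be used to compare the primary and secondary endpoints between the SJZD group and the placebo group", under intention-to-treat, and "The missing data will be filled by the method of the last observation carried forward". Neither rule exempts any endpoint.

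Trial status plans recruitment from January 2023 to June 2024 and the end of follow-up in September 2025.

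**The concern.** Two things interact. First, the year-2 outcome can be read as cumulative (an adenoma at Visit 4 or Visit 5) or as the finding at Visit 5 alone. Between the two visits some lesions are removed, and more will be removed in the arm with more year-1 recurrence. The two readings therefore measure different things and can give quite different numbers.

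Second, a patient without Visit 5 receives the Visit 4 status. Neither reading makes that a valid value for everyone:

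- **Visit 5 only:** a patient whose Visit 4 adenoma was removed is entered as having a recurrence at Visit 5. The year-1 comparison leaks into the year-2 comparison.
- **Cumulative:** a Visit 4 recurrence is rightly kept as an event, but every Visit-4-negative patient without Visit 5 is entered as recurrence-free through year 2, as if the second year carried no risk.

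The outcome is the trial's only efficacy evidence on recurrence after treatment stops. A difference, or part of one, could come from the filling rule alone.

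**Working it through.** The article gives no expected year-2 rate, so there is no figure to reproduce.

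**Inputs from the document.** 120 patients per arm and 10% dropout (Sample size); recurrence of 26.6% to 51.6% in earlier studies (Discussion); the calendar dates (Trial status).

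**Assumptions.** Year-1 rate *p* of 40% on placebo and 20% on SJZD; new recurrence in year 2, *h* = 20% in both arms, independent of year 1 (no drug effect after stopping); share *r* of year-1 lesions resected; share *m* missing Visit 5, equal in both arms. Differences are placebo minus SJZD.

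**1. The readings diverge without any missing data.**

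Visit 5 only = 1 − (1 − p(1 − r))(1 − h). Cumulative = 1 − (1 − p)(1 − h).

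| Reading | Placebo | SJZD | Difference |
|---|---|---|---|
| Visit 5 only, r = 1 | 20% | 20% | 0 |
| Visit 5 only, r = 0.5 | 36% | 28% | 8 points |
| Cumulative | 52% | 36% | 16 points |

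**2. LOCF under the Visit-5-only reading, r = 1.**

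Filled rate = (1 − m)h + m·p.

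- m = 10%: 0.9×0.20 + 0.1×0.40 = 22%, against 0.9×0.20 + 0.1×0.20 = 20%. Difference 2 points.
- m = 50%: 0.5×0.20 + 0.5×0.40 = 30%, against 0.5×0.20 + 0.5×0.20 = 20%. Difference 10 points.

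The true difference is 0, so the added amount is m × (year-1 difference): 0.1×20 = 2 and 0.5×20 = 10. At 120 per arm, the chance of a significant result favouring SJZD rises from 2.5% to about 6% and about 43%.

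With year-1 rates of 26.6% and 15.6% (an 11-point difference), the added amounts are 1.1 and 5.5 points.

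If the true Visit 5 difference is not zero, the shift is m × (year-1 difference − Visit 5 difference). With r = 0.5 and m = 50% it is 0.5×(20 − 8) = 6 points, so 8 becomes 14.

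**3. LOCF under the cumulative reading.**

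Filled rate = p + (1 − p)·h·(1 − m).

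- m = 10%: 0.40 + 0.60×0.20×0.9 = 50.8%, against 0.20 + 0.80×0.20×0.9 = 34.4%. Difference 16.4 points.
- m = 50%: 0.40 + 0.60×0.20×0.5 = 46%, against 0.20 + 0.80×0.20×0.5 = 28%. Difference 18 points.

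The true values are 52%, 36% and 16 points. Both rates are too low, and the difference moves towards the year-1 value of 20.

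**4. Unequal missingness can reverse the sign.**

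Take 51.6% and 40.6% at year 1, h = 20%, r = 1, with 5% missing on placebo and 15% on SJZD, read as Visit 5 only. Placebo: 0.95×0.20 + 0.05×0.516 = 21.6%. SJZD: 0.85×0.20 + 0.15×0.406 = 23.1%. The difference is −1.5 points where the truth is 0.

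**5. How much could be missing.**

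Recruitment spans 18 months. A month-24 endoscopy by September 2025 requires enrolment by about September 2023, the first 9 of those months. With uniform accrual (an assumption), 9/18 = 50% would lack it. A patient enrolled in June 2024 reaches month 12 in June 2025, so a Visit 4 status would exist for LOCF to carry.

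**The case against.** A reader might infer that resection at Visit 4 erases a real year-1 benefit. The document does not support that:

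- It does not fix a Visit-5-only rate. The outcome is anchored to the index polypectomy, and the Discussion speaks of recurrence rising with longer follow-up. Both fit a cumulative count, under which resection removes no event. The parallel wording of the primary outcome, and the explicit reference to either endoscopy in the second secondary outcome, lean the other way. Neither settles it.
- Resection depends on criteria. With half of the lesions removed, the Visit 5 difference is diluted to 8 points, not lost.
- Year-1 recurrence is the primary outcome and is tested separately. New adenomas after treatment stops are a legitimate question of their own. If the drug has no effect after stopping, a zero difference is the correct answer to it. The contrast between 0 and 16 points is between two estimands and is not evidence of bias.

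Two further objections carry weight. A condensed article may leave a counting rule to the full protocol or analysis plan. And at the planned 10% dropout, spread equally, LOCF moves the result by only about 2 points. Both limit the point, but the LOCF rule is stated, not omitted. The article's own dates could also take the missing share well beyond 10%.

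**Conclusion.** The point holds for the year-2 outcome. The counting rule is open, and the stated LOCF rule is unsuitable under either reading.

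Under the assumptions of 40% against 20% at year 1, full resection and 20% new recurrence in both arms, LOCF creates a Visit 5 difference of 2 points at 10% missing and 10 points at 50% missing where none exists. Under the cumulative reading it lowers both rates and moves a 16-point difference to 16.4 or 18 points. With equal missingness the error favours SJZD in these examples; with unequal missingness it can go either way.

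The 50% figure rests on uniform accrual and on the September 2025 date being meant literally. If Visit 5 endoscopies continue until every patient reaches month 24, missingness falls back to ordinary dropout and the effect is small.

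The definition of the primary outcome is not affected. This should be settled before unblinding.

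**What to change.** 1. State the main year-2 endpoint as at least one adenoma at Visit 4 or Visit 5, among all randomised patients. A Visit 4 recurrence stays an event whether or not Visit 5 takes place.
2. For Visit-4-negative patients missing Visit 5, replace LOCF with multiple imputation by arm and baseline factors, with a sensitivity analysis that varies the imputed recurrence risk by arm. State a matching rule for patients without a Visit 4 endoscopy. Compare arms on the estimate pooled over imputations.
3. Report adenomas new at Visit 5 separately, using the recorded location so that a Visit 4 lesion left in place is not counted as new.
4. Reconcile the end of follow-up with 24 months after the last enrolment. Imputation cannot make up for half the endoscopies without a large loss of precision.

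Items 1 to 3 cost wording and programming; the endoscopy data are already planned. Item 4 may extend the calendar. The downside of the cumulative endpoint is that it contains the primary-outcome events and so does not isolate the off-treatment effect, which is why item 3 is needed.

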### Randomization and blinding

Permuted block randomization, which is stratified by recruiting sites, will be used to allocate participants to the SJZD group or placebo group in a 1:1 ratio by the SAS statistical analysis system. All drugs will be sealed in identical opaque envelopes only labeled with a random code number. Participants will be enrolled by clinicians and receive an envelope in sequence. An independent statistician will finish the randomization. Clinicians, nurses, researchers and patients who participate in this trial will all be blinded to the treatment assignment. The random number and treatment assignments will be sealed and reserved by the principal investigators of this study. The blinding will not be unmasked until the trial and data analysis finish or in the event of serious AEs. Emergency letters sealed in opaque envelopes will be sent to each recruiting site. Assignment information and emergent conditions are contained in the letter. If any serious AEs occur, the emergency letter will be opened, and the corresponding patient will be withdrawn from the trial. A report of serious AEs should be submitted to the principal investigators within 24 h. The codes of treatments will be uncovered after the closure of follow-up and the specific intervention relevant to the cords will be uncovered after data analysis.

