#### Inclusion criteria

Participants will be eligible if they meet all of the following criteria:1. Individuals aged from 18 to 75 years, regardless of gender2. Individuals who underwent complete painless endoscopic adenoma resection (excluding hot polypectomy, hot snare polypectomy and argon plasma coagulation) within 2 weeks before recruitment3. At least 1 but no more than 6 CRAs confirmed by histology (including tubular, tubulovillous, and villous adenoma)4. Boston Bowel Preparation Scale (BBPS) score ≥7 points5. The score of SDS in TCM ≥20 points6. Individuals with adequate organ function7. Individuals who provide informed consent and can cooperate with long-term follow-up

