#### Withdrawal/termination criteria

Participants will be withdrawn or terminated from the trial if they meet any of the following criteria:1. Serious adverse events are reported at any time, and patients are unable to continue2. Patients who present with serious changes or complications related to the disease during the trial3. Patients who cannot comply with the instructions and follow-up procedures of this trial, leading to incomplete medical administration records, or patients who took banned drugs or other medications that may interfere with the efficacy and safety evaluation of this study4. Patients who request to be withdrawn from the trial

Besides, researchers will record the last time of drug intake and collect evaluation items of participants who discontinue or deviate from intervention protocols.

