### Interventions

#### Drug intervention

The intervention phase will last 12 months. Both SJZD and placebo are designed as granules with the same weight (1.77g/pack) and packaging. The appearance, texture, smell and taste of placebo granules are the same as SJZD granules but without any therapeutic effect. The granules in one package are dissolved in 200 mL of hot water. Patients are asked to take two packages orally two separate times in 1 day (3.54 g/day). There is no reduction or escalation of drug dose and frequency. SJZD and placebo are provided by Sichuan Neo-green Pharmaceutical Technology Development Co., Ltd. (Sichuan, China). The ingredients of placebo include one-tenth dose of SJZD (Radix ginseng, Rhizoma Atractylodis macrocephalae, Poria and Radix Glycyrrhizae Preparata) and maltodextrin. All the processing and preparation of medications and placebo are qualified. For participants who have severe adverse events (AEs) relevant to this trial, post-trial care will be arranged, and additional pecuniary compensation will be given. For participants who have adverse reactions not related to the drug in this trial, the relevant medical interventions will be implemented based on the comprehensive information of patients, including previous medical histories, symptoms and signs, laboratory, imaging and other examination results.

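### Any serious adverse event opens the code and ends trial participation, which is broader than the withdrawal criteria and can cost the month-12 primary endoscopy

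*Protocol article*

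**What the plan says.** Randomization and blinding gives the rule for a serious AE: "If any serious AEs occur, the emergency letter will be opened, and the corresponding patient will be withdrawn from the trial". The same section also names such an event as sufficient ground for unmasking: "The blinding will not be unmasked until the trial and data analysis finish or in the event of serious AEs". Neither sentence asks whether the event is related to treatment, whether care depends on knowing the assignment, or whether the patient could go on. The emergency letters are held at each recruiting site.

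Withdrawal/termination criteria opens with "Participants will be withdrawn or terminated from the trial if they meet any of the following criteria", and its first criterion reads "Serious adverse events are reported at any time, and patients are unable to continue". The section closes by saying that researchers will note the last drug intake and "collect evaluation items of participants who discontinue or deviate from intervention protocols".

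On outcome assessment, Study design and setting states: "Endoscopy will be conducted at the end of the intervention phase and 1 year later". Table 2 shows endoscopy at enrolment, visit 4 (month 12) and visit 5 only. The primary outcome is adenoma recurrence at the first year (Outcomes). Statistical analysis plans ITT, with missing data filled by LOCF.

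**The concern.** Two sections give a site different instructions for the same patient: one who has a serious AE, recovers, and is able and willing to go on. One section lets that patient stay. The other opens the code and removes the patient.

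Both sections also treat leaving the drug and leaving the trial as one act. The primary outcome depends on a single endoscopy at month 12, so removal before that visit can mean no primary outcome for someone who could have provided it. ITT needs outcomes on everyone randomised, whether or not they still take the drug. LOCF cannot supply a measurement here, because the only earlier endoscopy is the baseline one. If such removals were systematically more frequent in one arm, the filled values would bias the comparison. The code would also be opened at the site without any stated clinical need.

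**Working it through.** **Step 1. The two rules side by side.**

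| Patient with a serious AE | Withdrawal/termination criteria (plain reading) | Randomization and blinding |
|---|---|---|
| Cannot continue | Leaves the trial | Code opened, leaves the trial |
| Can continue | Stays | Code opened, leaves the trial |

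The rules differ in the second row. In the first row they agree on withdrawal, and it is withdrawal from the trial, not from study drug alone.

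**Step 2. What happens to the primary outcome.** Between enrolment and visit 4 no endoscopy is scheduled. A patient removed in that window has a year-1 result only if the closing sentence of Withdrawal/termination criteria is taken to include the month-12 endoscopy, which it does not say. Otherwise LOCF applies. The article does not say how LOCF codes this patient. Eligibility requires complete resection and excludes incomplete removal, so the last known state is adenoma-free, and the natural fill is no recurrence.

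**Step 3. Size.** The plan gives no serious-AE rate and no figure on this point to reproduce, so the rate, timing and split below are assumptions.

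Inputs from the article: 240 patients, 120 per arm, 10% dropout (Sample size); recurrence p from 26.6% to 51.6% (Discussion).

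Assumptions: 2% to 10% of patients have a serious AE over 24 months; events are evenly spread, so half precede month 12; every early case loses the endoscopy; cases split 2:1 between arms; there is no drug effect.

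- Serious AEs over 24 months: 0.02 × 240 = 4.8 to 0.10 × 240 = 24.
- Before month 12: 4.8/2 = 2.4 to 24/2 = 12.
- Share of the dropout allowance (0.10 × 240 = 24): 2.4/24 = 10% to 12/24 = 50%.
- Split 2:1: 1.6 against 0.8 patients, a loss difference of 0.8/120 = 0.67 points; up to 8 against 4, a difference of 4/120 = 3.33 points.
- Shift with adenoma-free coding = loss difference × p. Low end: 0.67 × 0.266 = 0.18 and 0.67 × 0.516 = 0.34 points. High end: 3.33 × 0.266 = 0.89 and 3.33 × 0.516 = 1.72 points. Apparent recurrence is lowered in the arm with more withdrawals.
- Standard error of the difference = √(2p(1−p)/120): 5.70 points at p = 0.266 and 6.45 points at p = 0.516.
- Largest shift in standard errors: 1.72/6.45 = 0.27. The two-sided type I error would then be about 5.8% instead of 5%.

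**Step 4. Why this is an upper bound.** Patients who truly cannot continue leave under either section. Only those able to continue are lost through the broader rule. If a fraction f of early cases could continue, at the same 2:1 split, the shift due to that breadth is f times the figures above; for example f = 0.5 gives at most 0.5 × 1.72 = 0.86 points. The documents do not allow f to be estimated.

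**The case against.** The strongest reply has four parts.

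First, the criterion "Serious adverse events are reported at any time, and patients are unable to continue" may be loose English for a consequence: a serious AE occurs and so the patient cannot go on. That reading would remove the conflict between the sections. It would not remove the unconditional opening of the code, or withdrawal from the trial where stopping the drug would do.

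Second, the sentence on collecting evaluation items sits under the withdrawal criteria. It naturally covers patients withdrawn for a serious AE, and nothing limits it to non-compliant patients or those who took banned drugs. This stands, and loss of the endoscopy is therefore possible rather than stated. But the sentence names no endoscopy and sits beside a rule that ends participation, so a site cannot tell that the patient should return at month 12.

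Third, the 2:1 split has no support in the documents, and a chance imbalance favours either arm equally. This also stands. The shift above is a bounding illustration, not an expected bias.

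Fourth, the unmasked patient leaves the trial, so no later blinded assessment of that patient is spoiled, and no effect on other patients is shown. That is fair. The unblinding matters mainly because it is unnecessary, and because it would become a problem once such patients are retained.

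A reader might go further in two ways that the documents do not support. One is to carry forward the index adenomas ("At least 1 but no more than 6 CRAs confirmed by histology") and score the patient as recurrent. Under the same assumptions that gives up to 3.33 × (1 − 0.266) = 2.45 points, or 2.45/5.70 = 0.43 standard errors. Those adenomas were completely resected, so counting them as recurrence contradicts the endpoint. The other is to see a contradiction with Drug intervention, which says "For participants who have adverse reactions not related to the drug in this trial, the relevant medical interventions will be implemented". That text concerns medical care and is silent on unblinding.

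**Conclusion.** The point holds in a limited form. Randomization and blinding requires code-breaking and trial withdrawal for any serious AE. The withdrawal criteria, read plainly, are narrower. Both end participation rather than treatment, and no text secures the month-12 endoscopy for a patient removed before it. Following the broader rule would discard primary outcomes that patients could still have given, which works against the planned ITT analysis.

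The size is unknown and probably small. Under an assumed 2% to 10% serious-AE rate, the 2 to 12 early cases lie within the 24 dropouts allowed for. A reader might infer that all of them are lost because of this rule, but only the subset able to continue is. With every early case lost, a 2:1 split and adenoma-free coding, the shift is at most about 1.7 points (0.27 standard errors). The case for change rests on avoidable data loss and avoidable unblinding that are cheap to prevent, not on a large expected bias.

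**What to change.** 1. Align Randomization and blinding with Withdrawal/termination criteria, so that a serious AE alone does not remove a patient.
2. Open the emergency letter only when the assignment is needed for clinical care.
3. Make a serious AE a reason to stop study drug only. For consistency with ITT, treat the other investigator-led withdrawal grounds the same way; a patient's own request to leave remains a withdrawal.
4. State that the month-12 and year-2 endoscopies are still done after the drug is stopped, unless consent is withdrawn or endoscopy is contraindicated.

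Items 2 and 3 belong together: once patients stay in, needless unblinding would affect someone whose outcome is still to be assessed.

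The cost is protocol wording and an instruction to sites. Both endoscopies are already scheduled for every patient. The downside is a small effort to retain patients who are off drug.
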